## Abstract

**Introduction::**

Chronic obstructive pulmonary disease (COPD) is a common high-burden and highly disabling lung disease. The quality of life and exercise endurance of patients with COPD is often low because of atrophy of the respiratory and skeletal muscles. Although recommended by the global initiative for chronic obstructive lung disease guidelines, pulmonary rehabilitation (PR) has not been used widely because of its inherent limitations. Tuna-Hui-Chun-Gong (TNHCG) is a popular traditional exercise used to treat COPD in China. We aim to evaluate the safety and efficacy of TNHCG for PR of COPD.

**Methods::**

The provided protocol is for a single-blind randomized controlled trial in which 120 COPD patients will be randomly and equally divided into the experimental or control group. The control group will be treated with standard COPD drugs while the experimental group will perform TNHCG exercises apart from standard drug treatment. The duration of treatment will be 24 weeks and a follow-up for 48 weeks. The primary outcome will be the 6-Minute Walk Test. The secondary outcomes will include the pulmonary function test, St George's respiratory questionnaire, COPD assessment test, modified medical research council dyspnea scale, Hospital Anxiety and Depression Scale, and exacerbation frequency. A safety assessment will also be performed during the trial.

**Discussion::**

Our study will provide evidence to support TNHCG exercise as an additional measure for PR of COPD.

**Trial registration::**

ChiCTR1900028332, Registered December 29, 2019.

**Ethics and dissemination::**

Ethics approval has been granted by the Sichuan Traditional Chinese Medicine Regional Ethics Review Committee (No. 2019KL-050).

## Introduction

1

Chronic obstructive pulmonary disease (COPD) is a chronic disease characterized by shortness of breath, chronic cough, and poor exercise tolerance.^[1]^ Although the symptoms of COPD can be well controlled with drugs, patients often end up having physiological dysfunctions and lower quality of life due to respiratory and skeletal muscle fatigue and atrophy. Consequently, pulmonary rehabilitation (PR) for COPD has recently gained importance. Numerous studies have confirmed that PR not only improves dyspnea, health status, quality of life, and exercise tolerance in patients with COPD, but also reduces hospitalization time for patients who experienced exacerbation and symptoms of anxiety and depression.^[2–4]^ Moreover, PR has been recommended in various versions of the global initiative for chronic obstructive lung disease (GOLD) guidelines.^[5]^ According to the definitions proposed by the American Thoracic Society and European Respiratory Society, PR refers to interventions that are performed after a comprehensive assessment of patients, and include education, sports training, nutritional support, and behavior change, with exercise being a key component of PR.^[6]^ The goal of PR is to improve the physical and psychological conditions of patients with chronic respiratory diseases and promote their long-term compliance with a healthy lifestyle. Previous studies have confirmed that traditional sport exercises such as Tai Chi, Yoga, Yi Jin Jing, and Wu Qin Xi promote PR of COPD patients and improve their lung function and quality of life.^[7–10]^ To date, however, there has been no high-quality clinical trial that assessed the effectiveness and safety of Tuna-Hui-Chun-Gong (TNHCG) exercise for rehabilitation of COPD.

TNHCG is mainly composed of Wudang, which originated from a Taoist health care sport named WuxingGong. It includes tortoise-shaped postures to help improve balance, posture alignment, weight shifting, circular movements, relaxation, and breath control. Compared to other exercises, tortoise-shaped posture exercises have simple moves and focus on breath control. Some studies showed that tortoise-shaped posture exercises improve 6-Minute Walk Test (6-MWT) scores, lung function, and COPD Assessment Test (CAT) score during the stable period of COPD.^[11–13]^ Apart from the tortoise-shaped posture exercises, TNHCG also includes lip contraction breathing, abdominal breathing, and acupressure, all of which improve PR for COPD as confirmed by previous studies.^[14–16]^ In our hospital, TNHCG has been widely used in PR of chronic lung diseases for many years. Clinical observation revealed that it improves symptoms, quality of life, and exercise endurance of patients with chronic lung diseases. However, whether it also plays an important role in lung rehabilitation of COPD is not clear. Nevertheless, it is reasonable to hypothesize that TNHCG will be effective for the rehabilitation of COPD. Therefore, we designed this randomized controlled trial to evaluate the efficacy and safety of TNHCG for the rehabilitation of COPD.

## Methods and design

2

### Design

2.1

The following is a protocol for a prospective randomized controlled clinical trial. The trial has been registered with the Chinese Clinical Trial Registry (no ChiCTR1900028332, registered December 29, 2019). After obtaining written informed consent, a 1-week run-in period will be implemented, after which 120 eligible participants will be randomly assigned to a trial group or a control group in a 1:1 ratio. The 2 groups will then undergo treatment for 24 weeks with follow-up after 12 weeks. The study procedure is shown in Figure 1. The trial aims to investigate the additional benefits and safety of TNHCG compared to conventional drug treatment for COPD. It will adhere to the Standard Protocol Items: Recommendations for Interventional Trials (SPIRIT) 2013 statement. The schedule of enrollments, interventions, and assessments is shown in Figure 2. The SPIRIT 2013 checklist is presented as Additional File 1.

**Figure 1 F1:**
[figure not shown]
Flow chart of the study design. 6MWT = 6-Minute Walk Test, CAT = COPD assessment test, mMRC = The Modified Medical Research Council Dyspnea Scale, SGRQ = St George's Respiratory Questionnaire.

**Figure 2 F2:**
[figure not shown]
SPIRIT figure: Schedule of enrollments, interventions, and assessments. 6MWT = 6-minute walk test, CAT = COPD assessment test, HADS = The Hospital Anxiety and Depression Scale, mMRC=The Modified Medical Research Council Dyspnea Scale, PFT = Pulmonary function tests, SGRQ = St George's Respiratory Questionnaire, [1] PFT: FEV1, Forced expiratory volume in one second; FVC, Forced volume capacity. [2] Laboratory tests: blood, urine, feces, electrocardiogram, and kidney and liver function tests.

### Ethics approval

2.2

The study is in compliance with the Declaration of Helsinki (Edinburgh 2000 version). The final amendments (version: November 4, 2019) and the consent form have been reviewed and approved by the Ethics Committee at Hospital of Chengdu University of Traditional Chinese Medicine (approval no: 2019KL-050). If there are any amendments to the protocol, approval will be sought again from the ethics committee.

### Recruitment

2.3

Participants will be recruited via an advertisement through media and based on the advice of respiratory doctors at the Chengdu University of Traditional Chinese Medicine hospital (Chengdu, China). Before enrollment, participants will be provided with detailed information about the clinical study, including its purpose, procedure, schedule, and possible risks and benefits. Only those who agree to sign the informed consent form will be included in the study.

### Sample size

2.4

Sample size calculations are based on the primary outcome (improvement in the 6-MWT). Referring to previous research by Chen et al,^[17]^ compared to the conventional treatment group, the 6-minute walking distance (6MWD) of the COPD TaiChi PR group improved by an average of 52 m (variance 77.5, correlation coefficient 0.7–0.8, power 0.90). Power analysis revealed that 96 participants, 48 in each group are required to attain a significance level of 2.5%. To avoid the decrease in sample size caused by follow-up drop-outs, the total sample size required, calculated with a 20% drop-out rate, is 120 participants with 60 participants per group.

### Randomization and blinding

2.5

A professional statistician with expertise in evidence-based traditional Chinese medicine in the Sichuan province will generate 120 random serial numbers using SAS 9.2 software (SAS, Cary, NC). Randomization will be performed after screening and baseline assessment, and eligible patients with COPD will be assigned to the trial group or the control group in a 1:1 ratio. The allocation sequence will be kept in sequentially numbered, sealed, and opaque envelopes. The envelopes will be kept safe and opened only by a designated administrator who will not directly participate in the recruitment or follow-up of any participant. The main investigator, data manager, data analyst, and outcome evaluators will be blinded to the group allocations. Participants and TNHCG instructors who supervise the exercise will not be blinded to the allocation. Once the groups are allotted, the TNHCG instructors will receive a copy of the participant number and allocation, and the outcome assessor will be informed of the participant number only.

### Diagnostic criteria

2.6

Participants must meet the diagnostic criteria mentioned in the GOLD guidelines^[5]^ (Table 1).

**Table 1 T1:**
[figure not shown]
Diagnostic criteria for chronic obstructive pulmonary disease^[5]^.

### Eligibility criteria

2.7

Inclusion criteria:

1.Patients aged 40 to 75 must meet the diagnostic criteria of COPD according to the GOLD guidelines; no gender and grade limitations.2.Patients with acute exacerbation periods must first be relieved before they can participate in the trial, while patients with stable COPD meet the inclusion criteria.3.Patients have no heart, liver, kidney, or mental system issues.4.Patients provide written informed consent.

Exclusion criteria:

1.Participants with other chronic respiratory diseases.2.Participants with severe comorbidities, such as tumors, symptomatic cardiovascular diseases, myocardial infarction, and neuromuscular diseases.3.Participants who are pregnant or lactating.4.Participants with AIDS, mental illnesses, and cognitive dysfunction.5.Participants who are currently practicing traditional Qigong exercises such as Baduanjin and TaiChi or are participating in other clinical trials associated with COPD.

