### Treatment plan

3.1

Participants in the 2 groups will receive the same kind of education about COPD. The contents include smoking cessation, nutrition support, inhalation techniques, coughing techniques, and knowledge of COPD.

The control group will only be treated with standard COPD drugs, while the trial group will perform TNHCG exercises apart from standard drug treatment.

Participants in the trial group will perform TNHCG exercises five times a week, totally 30 minutes per time, for 24 weeks. Before the start of the trial, a designated person (a nurse or rehabilitation physician not involved in conducting this study) will guide the participants on how to perform TNHCG exercises at our hospital. Participants will be required to practice until their movement and breathing are coordinated. If a patient is discharged from the hospital, a designated person will keep in touch with them and continue to guide them through telephone, video, and WeChat every week. The specific exercise content of TNHCG is shown in Figure 3.

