##### 6-Minute Walking Test

3.3.1.1

The primary outcome is the change in 6-MWD from baseline to the end of the treatment period (week 24). The purpose of this test is to measure the maximum distance that the participants can walk as fast as possible within 6 minutes on a flat surface. The 6-MWT is one of the most widely used tests to assess exercise tolerance in COPD.^[17]^ Participants will be given 400 μg salbutamol aerosol 20 min before the tests for safety.

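### Recently exacerbated and stable patients enter together, yet no stated stratum or covariate accounts for spontaneous recovery in the 24-week 6MWD change

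*Protocol article*

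**What the plan says.** **Entry.** Protocol article, Section 2.7, criterion 2: "Patients with acute exacerbation periods must first be relieved before they can participate in the trial, while patients with stable COPD meet the inclusion criteria". Criterion 1 adds "no gender and grade limitations". No minimum time since the exacerbation appears in the text.

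**Run-in.** Section 2.1: "a 1-week run-in period will be implemented, after which 120 eligible participants will be randomly assigned".

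**Setting.** Section 3.1 allows for participants who begin in hospital: "If a patient is discharged from the hospital, a designated person will keep in touch with them".

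**Allocation.** Section 2.5: "eligible patients with COPD will be assigned to the trial group or the control group in a 1:1 ratio". This happens after baseline assessment, from a list of 120 numbers held in concealed envelopes. No stratification factor is named.

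**Endpoint and analysis.** The primary outcome (Section 3.3.1.1) is week-24 6MWD minus baseline 6MWD. Section 3.8 compares the arms with a two-sample t test or a nonparametric alternative and names no covariate. It also plans paired tests of each measurement against its own baseline.

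**The concern.** A patient whose exacerbation has recently settled may start from a temporarily low walking distance, and from temporarily poor symptom scores and lung function. Such a patient may improve over the next weeks in either arm, while a stable patient would show less of this. A change-from-baseline endpoint takes in that recovery.

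Two things are at stake. First, the between-arm estimate becomes noisier, and in this one trial it may be shifted if recovering patients happen to fall unevenly. Baseline 6MWD alone does not fully deal with this, because the same low baseline can belong to a recovering patient or to a permanently limited one. Second, a significant before–after change within the trial arm could be read as benefit from the exercise when part or all of it is natural recovery.

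**Working it through.** **1. The plan's own figure.** The inputs from Section 2.4 are a difference of 52 m, 77.5 (labelled a variance, but workable only as an SD in metres), power 0.90 and a significance level of 2.5%. Taken as one-sided 2.5%, which equals the two-sided 5% of Section 3.8, the t-based size is 47.7, so 48 per arm. Then 96 / 0.8 = 120. The stated sizes reproduce.

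**2. Assumptions.** The documents give neither the share p of entrants still recovering nor their average spontaneous gain g. I take p = 0.3 and 0.5, and g = 40, 60 and 80 m. I also take 77.5 m as the SD of the change without recovery.

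**3. Between-arm precision.** SD = √(77.5² + p(1−p)g²), with 77.5² = 6006.25. The 1-SD shift in the estimate from uneven entry status is g × √(2p(1−p)/48). Power is t-based, two-sided 5%, for 52 m.

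| p | g (m) | p(1−p)g² | SD (m) | Power, 48/arm | Power, 60/arm | 1-SD shift, 48/arm (m) |
|---|---|---|---|---|---|---|
| – | 0 | 0 | 77.5 | 90.2% | 95.4% | 0 |
| 0.3 | 40 | 336 | 79.6 | 88.6% | 94.4% | 3.7 |
| 0.5 | 40 | 400 | 80.0 | 88.3% | 94.2% | 4.1 |
| 0.3 | 60 | 756 | 82.2 | 86.6% | 93.0% | 5.6 |
| 0.5 | 60 | 900 | 83.1 | 85.9% | 92.5% | 6.1 |
| 0.3 | 80 | 1344 | 85.7 | 83.7% | 90.9% | 7.5 |
| 0.5 | 80 | 1600 | 87.2 | 82.4% | 90.0% | 8.2 |

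A 2-SD imbalance doubles the last column, to about 7–16 m. The power loss and the shift describe the same quantity: the variance of the difference is 2 × (77.5² + p(1−p)g²)/48, and its second part is the chance imbalance. They should not be counted twice.

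**4. The other reading of 77.5.** Section 2.4 also gives a correlation of 0.7–0.8. If 77.5 m is the SD at one time point, the change SD is 77.5 × √(2(1−r)), which is 60.0 m at r = 0.7 and 49.0 m at r = 0.8. In the worst row (p = 0.5, g = 80) the SD becomes √(60.0² + 1600) = 72.1 m or √(49.0² + 1600) = 63.3 m. Power at 48 per arm is then about 94% or 98%.

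**5. Error rates with no treatment effect.** Simulation with 48 per arm and an assumed change SD of 50 m:
- p = 0.3, gain 50 m (mean change 0.3 × 50 = 15 m in each arm): the between-arm t test rejects in 4.9% of trials and the within-arm paired test in 46%.
- p = 0.5, gain 75 m (mean change 37.5 m in each arm): 5.2% and 98%.

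The randomized comparison keeps its level. The before–after tests detect recovery, which is a real change but not a treatment effect.

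**The case against.** The strongest reply is that this is a randomized trial with concealed allocation and a concurrent control arm on the same standard drugs. Recovery occurs in both arms, its expected contribution to the difference is zero, and the t test's standard error already reflects chance imbalance. That stands. A reader might infer that recovery is unbalanced between the arms or that the treatment effect is biased. The documents support neither: they show only that balance is not secured by a named stratum or covariate.

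The size can also be disputed. Section 3.8 plans intention to treat with missing values filled in, so 60 per arm may enter the test, and power is then 90–94% in every row. Filled-in values may dilute the effect, but that is a separate matter. The smaller change-score SD in step 4 also removes the shortfall. Both points stand.

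Three further inferences go too far:
- The sentence in Section 3.1 about discharge is conditional. It allows for inpatients but does not say how many there are.
- The Introduction's evidence "during the stable period of COPD" concerns tortoise-shaped posture exercises, one component of TNHCG, and not TNHCG as a whole.
- Run-in and baseline both precede randomization, but their order belongs to the Figure 2 schedule, which is not shown. Baseline may already be taken at the end of the run-in.

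Finally, a working definition of *relieved*, strata or covariates may sit in the full protocol or analysis plan, so their absence here is not itself the point. What remains is that the tests this article does state are unadjusted and include before–after comparisons that recovery can drive. Admitting both kinds of patient is a legitimate choice of a broad population, and the analysis should take it into account.

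**Conclusion.** The point holds as one of precision and interpretation. The stated entry rule mixes recently exacerbated and stable patients, and the stated allocation and analysis do nothing with that information.

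Under the assumed 30–50% share and 40–80 m gain, with SD 77.5 m and 48 per arm, about 2 to 8 percentage points of power are lost (from 90% to 82–89%), and a 1-SD imbalance moves the estimate by about 4–8 m. At 60 per arm or with a change SD of 49–60 m, power stays at about 90% or more. The share, the gain and the premise that recovery occurs at all are assumptions.

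The within-arm paired tests are the weaker part of the plan. Under no treatment effect they can reject in about half to nearly all trials, so they cannot support a claim of efficacy. The between-arm conclusion is not invalidated.

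**What to change.** 1. Record entry status for every patient: recent exacerbation or hospital stay, with its end date, versus stable. For patients already randomized, take it from pre-randomization records, by staff who do not know the allocation.
2. Analyse week-24 6MWD by ANCOVA with treatment arm, baseline 6MWD and entry status in the model. Treat the symptom scores in the same way, each with its own baseline. Fix this before the data are unblinded.
3. Base efficacy conclusions on the between-arm comparison, and label the within-arm paired tests as descriptive.
4. The investigators should clarify what *relieved* means in criterion 2. No interval is proposed here.
5. Stratifying the remaining allocations by entry status is optional. Recruitment is under way (Section 5.1), so it would leave a mixed scheme, and the covariate already does most of the work.

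The cost is one CRF field, one model term and a little retrospective data collection, with no extra patients. Section 2.2 sends protocol amendments back to the ethics committee, so a short submission should be expected.

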### Termination and withdrawal criteria

2.8

All participants will be informed that they have the right to withdraw from the trial at any point and that they will be provided with standardized treatment if they withdraw. The reason for withdrawal will be recorded in their case report file. The criteria for stopping treatment and withdrawing patients from the clinical trial are as follows: the participant developed adverse event due to TNHCG exercise, and the investigator believes it is not appropriate for them to continue the trial; the participant developed severe exacerbation of COPD; the participant developed another severe disease that needs to be treated during the study; poor compliance; the patient participated in another similar trial simultaneously.

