##### Exacerbation frequency

3.3.2.6

The number of acute exacerbation episodes of COPD (at week 36). COPD exacerbation is defined as an acute worsening of respiratory symptoms resulting in the requirement of additional therapy.^[22]^

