### Statistical analysis

3.8

All analyses will be conducted according to the intention to treat principle. Missing values will be replaced by the last observation carried forward method. Two similar participants with complete data will be double-checked to make sure that data are correct before analysis.

The data will be analyzed using the Statistical Package for the Social Sciences version 23.0 (SPSS 23.0, Chicago, IL). The analytical methods will be selected according to the distribution characteristics of the data: measurement data will be analyzed using group *t* tests or nonparametric tests, while count data will be analyzed using a Chi-square test or the Fisher exact probability method. Grade data will be analyzed using nonparametric tests. Compared with baseline values, measurement data will be assessed using paired *t* tests or nonparametric tests, and count data will be examined using a nonparametric test. All statistical tests will be bilateral tests and *P*-values <.05 will be considered statistically significant.

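### Section 2.8 uses one list both to stop treatment and to withdraw patients from the trial, so severe exacerbation, other severe disease, poor compliance or (on the investigator's judgement) a TNHCG-related adverse event ends follow-up

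*Protocol article*

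**What the plan says.** Section 2.8 introduces its list with "The criteria for stopping treatment and withdrawing patients from the clinical trial are as follows". The entries are:

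- an adverse event attributed to the exercise, if in the investigator's judgement the patient should not go on;
- severe exacerbation, with no condition attached;
- two further unconditional reasons, given as "the participant developed another severe disease that needs to be treated during the study; poor compliance";
- joining another similar trial at the same time.

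For those who leave, 2.8 mentions standardised treatment and a recorded reason. It describes no status in which a patient is off the exercise but still assessed.

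Four other sections bear on this:

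- Section 3.3.1.1 sets the primary outcome as the change in 6-minute walk distance (6MWD) from baseline to week 24.
- Section 3.3.2.6 counts acute exacerbations at week 36.
- Section 3.8 states "All analyses will be conducted according to the intention to treat principle" and, on missing data, "Missing values will be replaced by the last observation carried forward method".
- Section 3.5 commits researchers to try to follow randomised patients throughout, and monitors adherence at each visit.

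**The concern.** Stopping an exercise programme is a treatment decision. Leaving the trial is a data decision. Section 2.8 ties the second to the first.

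The triggers arise after randomisation and relate to how the patient is doing. Severe exacerbation is itself part of a secondary outcome, and poor compliance marks patients whose real outcomes an intention-to-treat comparison needs. The triggers are also not fully balanced between arms. A TNHCG adverse event can occur only in the TNHCG arm, and only that arm has an exercise prescription (section 3.1).

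At stake are two things:

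- **Primary outcome.** A patient withdrawn before week 24 enters the analysis with an earlier value in place of the week-24 distance, although some could still have walked. The missing data are avoidable and may be informative.
- **Exacerbation count.** The severe episode that triggers withdrawal can still be counted, but later episodes up to week 36 are not. The count is cut short in patients who have already had a severe event.

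**Working it through.** **Setting the sections side by side**

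1. Section 2.8 applies the same criteria to stopping treatment and to withdrawing from the clinical trial. Because both actions are named, the second cannot easily be read as merely repeating the first.
2. Section 3.5 promises an effort at full follow-up, in general terms. It does not say that patients withdrawn under 2.8 keep their visits.
3. Section 3.6 (Adverse events) stops only the intervention after a serious adverse event and does not mention leaving the trial. The article therefore separates the two actions there but merges them in 2.8.
4. Section 3.8 keeps everyone in the analysis and fills gaps by last observation carried forward. A withdrawn patient stays in the intention-to-treat set, but with a substituted value.

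The point rests on this comparison. The arithmetic below only gives a sense of scale.

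**The plan's own figures (section 2.4)**

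Inputs: difference 52 m; 77.5, labelled a variance but workable only as an SD in metres; power 0.90; significance level 2.5%, taken as one-sided, which equals the two-sided 5% of section 3.8.

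- Normal approximation: n per arm = 2 × (1.960 + 1.282)² × 77.5² / 52² = 46.7, so 47.
- Exact t test: power is 0.896 at 47 per arm and 0.902 at 48, so 48 per arm and 96 in total, as stated.
- Drop-out: 96 / (1 − 0.20) = 120, or 60 per arm. The allowance is 60 × 0.20 = 12 per arm.

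**Scale for the primary outcome (k and D are assumptions)**

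Suppose k of 60 patients in one arm have a carried-forward 6MWD that differs by D metres from their true week-24 value. The arm mean shifts by k × D / 60.

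| k | D (m) | Shift (m) | Share of 52 m |
|---|---|---|---|
| 6 | 26 | 2.6 | 5% |
| 12 | 26 | 5.2 | 10% |
| 6 | 52 | 5.2 | 10% |
| 12 | 52 | 10.4 | 20% |

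The sign is open. Carrying forward a value from before any gain understates benefit; carrying forward an early gain that is later lost overstates it. Equal errors in both arms cancel to 0 m in the group difference.

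The D = 52 rows, placed in the TNHCG arm with no gain carried forward, give observed differences of 46.8 m (k = 6) and 41.6 m (k = 12). Exact t-test power with 60 per arm at two-sided 5% is then 0.907 and 0.830, against 0.954 with no error. This is an unfavourable corner: it supposes that patients who stop exercising would still have reached the full 52 m.

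**Scale for the exacerbation count (rates are assumptions)**

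Take severe exacerbations as Poisson over 36/52 of a year, with follow-up ending at the first. Each patient then contributes at most one severe episode, with probability 1 − exp(−rate × 36/52).

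| Severe rate per year, control / TNHCG | Withdrawn, control / TNHCG | True ratio | Ratio as counted |
|---|---|---|---|
| 0.30 / 0.20 | 18.8% / 12.9% | 0.667 | 0.689 |
| 0.50 / 0.35 | 29.3% / 21.5% | 0.700 | 0.735 |
| 1.00 / 0.70 | 50.0% / 38.4% | 0.700 | 0.769 |

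Under these assumptions the cut-off pulls the ratio towards 1. The table covers severe episodes only.

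**The case against.** The strongest reply is that 2.8 never says assessments end. Section 3.5 promises follow-up with no exception for withdrawn patients, section 3.6 treats stopping the intervention as an action of its own, and a condensed article may leave visits after discontinuation to the full protocol. This makes the intention less certain. It does not remove the stated rule, which speaks of withdrawal from the trial, and neither section exempts patients who meet it. If only stopping treatment was meant, the same edit is needed to say so.

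Several narrower points stand:

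- Arm-specificity is complete only for the TNHCG adverse event. Both arms take standard drugs, so poor compliance could apply in either.
- Some patients with a severe exacerbation or another severe disease could not safely do a walk test, so not all the loss is avoidable.
- No effect on the primary result is demonstrated, and the power figures above do not isolate the harm from ended follow-up.
- Part of the 6MWD consequence comes from last observation carried forward and should not be counted twice if that method is criticised separately. What belongs to 2.8 is creating gaps that need not exist and losing later exacerbations.

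**Conclusion.** The concern holds. Followed as written, 2.8 takes randomised patients out of assessment for outcome-related or adherence-related reasons. That undercuts the intention-to-treat aim of 3.8 and the follow-up effort of 3.5, without formally contradicting either. Poor compliance is the clearest case, since it carries no evident safety reason to stop measuring.

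The size and direction of any bias cannot be determined, because the article gives neither rates for the criteria nor distances after withdrawal. The 2.6 to 10.4 m range rests on assumed k and D and is not an estimate. The conclusion depends on reading withdrawal from the trial in its ordinary sense, so confidence is medium. The change should be made, but the point does not show that the primary result is invalid.

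**What to change.** Reword 2.8 so that the list gives reasons to stop the exercise only. State that participants in both arms remain in follow-up unless they withdraw consent, with the week-24 6MWD collected where the walk test is clinically safe and exacerbations counted to week 36. Record poor compliance as a protocol deviation, using the adherence monitoring already in 3.5. Which clinical events should stop the exercise remains for the investigators.

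The cost is low: a wording amendment with the ethics approval that 2.2 already requires, plus some retention effort for patients who stop exercising. The assessments are already planned and the sample size does not change. Some walk tests will still be missed for safety, so missing data are reduced, not removed. Section 5.1 says recruitment is under way, and an assessment missed after withdrawal cannot be recovered, so the amendment should come before more patients are withdrawn.
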